### Sample size

Sample size calculations are based on detecting a 20% difference in the primary outcome of average daily SEDs between intervention and control arms, in each of the low- and the high-risk phenotype groups. There is currently no consensus as to a ‘safe’ daily SED limit. Instead, skin cancer prevention strategies for the public primarily aim to shift the distribution of sun exposures downwards, especially in seasons of peak exposure. Due to the skewed nature of the SED exposure data, the sample size was calculated using a *t* test with a geometric mean ratio (geometric mean SEDs in intervention group/geometric mean SEDs in control group) of 0.8, coefficient of variation 0.9, 80% power and *α* of 0.05.

Based on these calculations, a sample of 756 people (378 in the high-risk phenotype group and 378 in the low-risk phenotype group), split evenly between the intervention and control arms, will provide 80% power to detect a 20% reduction in the primary outcome in favour of the intervention with either low- or high-risk phenotypes. Allowing up to 15% with incomplete follow-up at 12 months, we will need to recruit 892 people (446 in each of intervention and control arms). Secondary analysis pooling the data from the low- and high-risk phenotype groups will give > 97% power to detect a 20% difference in SEDs between the intervention and control groups.

No interim analysis, safety analysis and or data monitoring is planned for this study due to the minimal risks associated with the intervention.

### General considerations for statistical analysis

The analysis principles are as follows:
All analyses will be conducted on an intention-to treat basis. All randomised participants will be analysed in the group to which they were assignedThe primary analyses will stratify by phenotypic risk category (high, low)Statistical hypothesis tests will be evaluated at a nominal two-sided 5% level of significanceIntervention effect estimates (i.e. difference in means, odds ratio or relative risk) and their 95% confidence interval (CI) will be reported for all outcomesThe assessment of the overall intervention effect on outcome measures will be adjusted for baseline scores and randomised stratification factorsSubgroup analyses will be carried out irrespective of whether there is a significant effect of intervention on outcome*P* values will not be adjusted for multiple comparisons.*P* values will be reported to three decimal places unless the *P* value is less than 0.001, in which case it will be reported as ‘ < 0.001’. The mean, standard deviation (SD) and any other statistics other than quantiles will be reported to one decimal place greater than the original data. Quantiles, such as median, or minimum and maximum will use the same number of decimal places as the original data. Estimated parameters, not on the same scale as raw observations (e.g. regression coefficients), will be reported to three significant figuresAnalyses will be conducted primarily using SAS, version 9.4 or later and R 3.6.1 or later

### Timing of analyses

The final analysis will be performed after all randomised participants have completed their 12-month follow-up (or dropped out prior to this).

### Analysis populations

The final analysis will include all participants who were randomised. The analysis population will be split into one of two phenotypic risk groups (i.e. high-risk and low-risk) as per the randomisation stratification variable ‘Traditional phenotypic risk score’. For secondary analysis of the primary outcome the analysis population will comprise the pooled phenotype risk groups.

### Covariates and subgroups

The following subgroup analyses will be performed in each phenotypic risk groups and overall. It is hypothesised that the effect of the intervention on behaviour change or psycho-social outcomes may be influenced (moderated) by:
Sex: male/other vs. femaleAge: 18–44 vs. 45–69 yearsState or territory of residence (based on latitude): QLD, NT, WA, NSW, ACT vs. SA, VIC, TASHealth literacy and numeracy: higher vs. lower [28]Family history of melanoma or a personal history of non-melanoma skin cancer: yes vs. noEducation: school-only vs. higher educationSocio-Economic Indexes for Areas (SEIFA) using the Index of Relative Socio-Economic Advantage and Disadvantage (IRSAD) based on postcode of residence and categorised into five groups using quintile cut-pointsChildren: yes vs. noRisk taking propensity: risk-averse vs. risk-seeking (see the Domain-specific Risk-taking (DOSPERT) scale below [37])Taking medications such as immuno-suppressants that may increase their sensitivity to sunlight (yes, no, don’t know)Genetic determinism, measured as *How much do you think genetic make-up, that is characteristics that are passed down from one generation to the next, determine whether or not a person will develop melanoma?* [38] on a 5-point Likert scale and categorised as 4 or 5 (completely/moderately) vs. 1, 2, or 3 (not at all, slightly, somewhat)Genomic risk category (available for the intervention group only): higher than average vs. average vs. lower than average riskDiscordant genotype/phenotype groups (available for the intervention group only):
◦ low-risk phenotype but high-risk genotype◦ high-risk phenotype but low-risk genotype◦ concordant combinations

DOSPERT: The Domain-specific Risk-taking (DOSPERT) [37] scale contains three separate constructs: ‘risk-taking’, ‘risk-perceptions’ and ‘risk-attitude’ across separate domains. Two domains of risk, ‘Health and Safety’ and ‘Social’ were shown to be relevant to a preventive intervention for sun-protection behaviours in our pilot study [39] and were included in the baseline questionnaire; the items are shown in Table 3. For the assessment of:
Risk-taking – participants were asked to indicate ‘The likelihood that you would engage in the described activity’, from extremely unlikely to extremely likely on a 7-point scaleRisk perception – participants were asked to indicate ‘How risky you perceive the described situations’ from not at all risky to extremely risky on a 7-point scaleRisk attitude – participants were asked to indicate ‘The benefits that you would obtain from each situation’, from no benefits at all to great benefits

**Table 3 Tab3:** Domain-Specific Risk-Taking (DOSPERT) domain subscales

Domain subscale	Item text
Health/safety	Drinking heavily at a social function
	Engaging in unprotected sex
	Driving a car without wearing a seat belt
	Riding a motorcycle without wearing a helmet
	Sunbathing without sunscreen
	Walking home alone at night in an unsafe area of town
Social	Admitting that your tastes are different from those of a friend
	Disagreeing with an authority figure on a major issue
	Choosing a career that you truly enjoy over a more prestigious one
	Speaking your mind about an unpopular issue in a meeting at work
	Moving to a city far away from your extended family
	Starting a new career in your mid-thirties

Item responses will be summated to obtain subscale scores for each domain for ‘risk-taking’, ‘risk-perceptions’ and ‘risk-attitude’. Individuals will be classified as ‘risk seeking’ if their subscale score was more than 1 SD above the mean; ‘risk averse’ if their subscale score was more than 1 SD below the mean; ‘risk neutral’ if their subscale score was within 1 SD of the mean.

### Missing data

The number of participants who complete the 12-month follow-up will be described by allocation; the study arms will be compared using chi-square tests and logistic regression to see if the attrition rate differs by arm and to compare baseline characteristics of participants who did and did not complete follow-up. Of those who complete follow-up, each variable will be examined for the presence of missing data and if > 10% is observed for primary or secondary outcomes, then sensitivity analyses will be performed using complete case analysis or multiple imputation methods assuming data are missing at random (MAR). The MAR assumption indicates that the propensity for missingness does not depend on the unobserved outcome but rather is related to some other observed data.

The distribution of dosimeter sun exposure days will be described by study arm. Non-adherence will be defined as participants that fail to wear the dosimeter over at least one day on both a weekday and a weekend. Level of adherence (e.g. number of days worn) will also be described. For participants who do not have UV dosimeter (SED) data for both weekday and weekend exposures, we will estimate their missing exposure using imputation methods based on the participant’s available weekday or weekend SEDs, and SEDs data from the same age-group, gender, traditional (phenotypic) risk group and state or territory.

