### Primary efficacy analysis

Geometric mean score and 95% CI will also be represented graphically from over time (baseline, follow-ups 1 and 2). The primary analysis will be an intention-to-treat comparison of intervention and control arms for mean differences in UVR exposure measured as log-transformed daily SEDs at 12 months. The primary efficacy of the intervention will be assessed in each phenotypic risk group (high and low). UV dosimeter values will be log-transformed because of their right-skew distribution, and log-transformed values will be interpreted as a percentage change in the geometric mean of SEDs/day [41]. An analysis of covariance (ANCOVA), adjusted for baseline values and all randomised stratification factors will be performed [40]. A sensitivity analysis will be conducted on the subgroup of participants (*N* = ~ 240) that will wear a UV dosimeter for 10 days at follow-up 1 (see subheading 'Sensitivity Analysis'); given the repeated nature of the outcomes in this subgroup, generalised linear mixed models (GLMMs) with random intercepts will be fitted to assess the overall intervention effect. The primary analysis will be based on the complete case principle given that the power was adjusted with a conservative loss to follow-up rate of 15%. However, if 10% or more of the randomised patients do not have their primary outcome recorded, a sensitivity analysis will be performed using multiple imputation methods assuming that data are missing at random.

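### The two 10% triggers for the missing-data sensitivity analysis are not harmonised, and for secondary outcomes dropout never counts towards one

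*SAP article*

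**What the plan says.** **Missing data section.** The trigger reads "Of those who complete follow-up, each variable will be examined for the presence of missing data and if > 10% is observed" for a primary or secondary outcome. If it is met, "sensitivity analyses will be performed using complete case analysis or multiple imputation methods assuming data are missing at random". Attrition is compared by arm, and the baseline characteristics of people with and without follow-up are compared, but no further analysis follows from the result. The section also imputes a missing weekday or weekend dosimeter value from the participant's other values and from similar participants.

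**Primary efficacy analysis section.** The comparison is called intention-to-treat, and "The primary analysis will be based on the complete case principle given that the power was adjusted" for a 15% loss. A second trigger follows, for the primary outcome only: "if 10% or more of the randomised patients do not have their primary outcome recorded, a sensitivity analysis will be performed", by multiple imputation under MAR.

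**Analysis populations section.** "The final analysis will include all participants who were randomised". General considerations for statistical analysis likewise says that everyone randomised is analysed as assigned.

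**Secondary efficacy analyses section.** With three time points, continuous outcomes use mixed models with random intercepts and binary outcomes use GEE with a log link. With two time points, continuous outcomes use ANCOVA and binary outcomes a log-link GLM. No separate missing-data rule is given here, so the Missing data section is the only one that applies to secondary outcomes.

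**The concern.** The two triggers differ in denominator (completers or randomised), in threshold (above 10%, or 10% and above), in outcomes covered and in method. The denominator is the difference that matters. Restricting the count to people who completed follow-up removes dropouts, who are the most likely source of missing 12-month data, before the count is made.

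Only the intervention arm receives a personal genetic risk booklet and a counsellor's call, so reasons for leaving could differ between arms. The SAP gives no data on this, but it takes the possibility seriously enough to compare attrition by arm. For secondary outcomes that comparison leads to no further analysis.

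The method list adds a smaller problem. Where the main analysis already uses complete cases, a sensitivity analysis by complete case can be met by running the same model again. The reason given for the complete-case primary analysis is that the sample size was inflated. Inflation protects power, but does not protect against selective loss.

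**Working it through.** **Inputs from the SAP (Sample size; General study design and plan; General considerations).** Geometric mean ratio 0.8, coefficient of variation 0.9, power 80%, two-sided alpha 0.05, 1:1 allocation, two phenotype groups, up to 15% incomplete follow-up, 756 evaluable, 892 recruited.

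**Step 1: reproduce the plan's figures.**
- Log-scale difference: |ln 0.8| = 0.2231.
- Log-scale SD: √ln(1 + 0.9²) = √ln 1.81 = 0.7703.
- The two-sample t test (noncentral t) needs 189 per arm per phenotype group, with power 0.802. 4 × 189 = 756, as stated.
- Dropout: 189 / 0.85 = 222.4, rounded up to 223 per cell. 4 × 223 = 892, as stated.

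The 15% is therefore a fair working figure for the check, read as an upper allowance.

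**Step 2: apply both triggers at 15% loss.**
- Dropouts: 0.15 × 892 = 133.8, about 134. Completers: 892 − 134 = 758.
- Randomised-based trigger (primary outcome): 10% of 892 = 89.2, so 90 missing are needed. 134 exceeds 90, and multiple imputation is required.
- Completer-based trigger (all outcomes): 10% of 758 = 75.8, so at least 76 completers must lack the outcome. Dropouts contribute nothing. With no other missing data the rate is 0% and the rule is silent.

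**Step 3: how much can be missing for a secondary outcome without a sensitivity analysis?** The SAP gives no figure for missing data among completers, so let x be that proportion and d the dropout proportion. The share of randomised participants without the outcome is 1 − (1 − d)(1 − x).

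| Dropout d | x = 0 | x = 10% |
|---|---|---|
| 5% | 5.0% | 14.5% |
| 10% | 10.0% | 19.0% |
| 15% | 15.0% | 23.5% |

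At d = 15%, x = 5% gives 19.25%. In every cell x does not exceed 10%, so the completer-based rule does not fire. In whole people at d = 15%, the most that escapes is 134 + 75 = 209, and 209 / 892 = 23.4%.

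**Step 4: which secondary outcomes are exposed?**
- *Two time points.* Time-specific UV exposure comes from the dosimeter, worn at 1 month by only about 240 participants (240 / 892 = 27%). For most people it has baseline and 12-month values only. ANCOVA drops anyone without the 12-month value.
- *Binary, three time points.* Standard unweighted GEE is not in general valid under MAR, which is the assumption the SAP names.
- *Continuous, three time points.* The mixed model keeps people seen at 1 month but not at 12 months, and is valid under MAR if correctly specified. Those with no follow-up at all still add nothing about the 12-month effect.

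**The case against.** Four replies have force.

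1. **The primary outcome is protected.** A reader might infer that the dropout allowed for would never lead to a sensitivity analysis. The document does not support that: the Primary efficacy analysis section counts "if 10% or more of the randomised patients do not have their primary outcome recorded", and at 15% loss this requires multiple imputation. This stands in full.

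2. **The rules do not command opposite things.** Each says what to do if its condition is met. Neither forbids imputation otherwise, so both can be followed, with the more specific one governing the primary outcome. This also stands: the triggers overlap and are unharmonised, but they are not incompatible.

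3. **The mixed models already use partial follow-up.** For continuous questionnaire outcomes this is right, so it would be too strong to say that every secondary outcome is unprotected. It does not help the two-time-point outcomes, the GEE outcomes or people with no follow-up. Complete case would likewise be a genuinely different analysis for the mixed-model and GEE outcomes. It repeats the main analysis only where that is already complete case, and even for the primary outcome it could differ if people with a partly imputed SED were left out.

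4. **Intention-to-treat against complete case is mostly labelling.** One might read the statement that all randomised participants are included as a contradiction that leaves the primary analysis unknown. The Primary efficacy analysis section says plainly what will be run, so a qualifier is enough.

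It is also fair to say that 15% is an upper allowance, which the SAP itself calls conservative, and that multiple imputation under MAR does not address dropout that depends on unobserved outcomes. The first affects the size of the gap. Neither justifies leaving dropouts out of the count.

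**Conclusion.** The concern holds for secondary outcomes. Because the only rule for them counts missing values among completers, dropout alone can never trigger a sensitivity analysis, whatever its size. At the 15% allowance, and assuming just under 10% missing among completers, about 23% of randomised participants could lack an outcome without one. With no missing data among completers the figure is 15%. The exposed outcomes are chiefly the two-time-point ones, including time-specific UV exposure, and the binary GEE ones.

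For the primary outcome what remains is tidying: two triggers where one would do, a method left open in one section, an analysis population stated more widely than the analysis, and no statement of whether a partly imputed SED counts as a complete case or as a recorded outcome. This is a should-fix: the primary result already has its safeguard at the planned loss, but the change would alter which secondary sensitivity analyses are run.

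**What to change.** - **One trigger** for primary and secondary outcomes: 10% or more of all randomised participants lacking the 12-month outcome.
- **One method:** multiple imputation under MAR, by arm, using the baseline value, the minimisation factors and available 1-month values. Note that 1-month dosimeter values exist for only about 240 participants, so they help little for UV outcomes.
- **Remove complete case** as a sensitivity option wherever the main analysis is already complete case.
- **Qualify** General considerations and Analysis populations to say that the primary analysis covers randomised participants with a 12-month SED, analysed as assigned. State whether participants with an imputed weekday or weekend SED belong to that set, and whether they count as recorded for the trigger.
- **Do not rest** the complete-case choice on the sample size inflation.

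The cost is a few sentences in the SAP and a modest amount of imputation work across the secondary outcomes that meet the trigger. No new data are needed.

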### Outcome measures

#### Primary outcome measure

The primary outcome for this study is total daily Standard Erythemal Doses (SEDs) measured 12 months after the baseline assessment (baseline questionnaire and UV dosimeter). A SED is an objective measure of UV exposure, measured using a time-stamped electronic dosimeter badge, mounted in light-weight, custom-made wristbands attached to the left wrist (similar to wearing a watch) during daylight hours [16]. UV dosimetry is the gold standard for assessing personal UV exposure [17, 18]. UV dosimeters will be worn by all participants for 10 days at baseline, and again 12 months after baseline. A subgroup of ~ 240 participants will also wear a UV dosimeter 1 month after receipt of the booklet/s. Total daily SEDs will be calculated as the weighted average of the average daily weekday and weekend SEDs (i.e. (weekday× 5 + weekend× 2)/7). SED values will be log-transformed for all analyses.

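### The rule for filling a missing weekday or weekend SED leaves out randomised arm and date of wear, and the plan does not say whether filled participants enter the complete-case primary analysis

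*SAP article*

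**What the plan says.** **Outcome.** Under Primary outcome measure: "Total daily SEDs will be calculated as the weighted average of the average daily weekday and weekend SEDs", with weights 5/7 and 2/7. Without both components there is no total. On wear: "UV dosimeters will be worn by all participants for 10 days at baseline, and again 12 months after baseline".

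**Filling a missing component.** Under Missing data, for participants without both day types, "we will estimate their missing exposure using imputation methods based on the" participant's "available weekday or weekend SEDs", together with "SEDs data from the same age-group, gender, traditional (phenotypic) risk group and state or territory". The four peer variables correspond to the minimisation factors under Randomisation and blinding. Arm and date of wear are not named. Nor is the method: it could be a mean, a ratio, a regression or a hot deck, and single or multiple.

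**Who is analysed.** Under Primary efficacy analysis: "The primary analysis will be based on the complete case principle". Multiple imputation follows as a sensitivity analysis "if 10% or more of the randomised patients do not have their primary outcome recorded". Missing data gives complete case a different role: if more than 10% is missing among those who complete follow-up, "sensitivity analyses will be performed using complete case analysis or multiple imputation methods". No section says on which side of the complete-case line a participant with one filled component falls.

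**The concern.** The primary model estimates an arm effect on log SED at 12 months. If part of that outcome is predicted from variables that omit arm, the predicted part need not carry the full arm difference, and the contrast can be diluted. Each phenotypic risk group is sized for 80% power with nothing to spare, so even mild dilution comes straight off the power.

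UV exposure is seasonal. The Sample size section refers to seasons of peak exposure, and a sensitivity analysis compares two spring/summer periods. Peers measured at another time of year are therefore poorer predictors.

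The undefined status of filled participants means that two statisticians following the SAP could analyse different sets. The SAP has a second statistician independently reproduce the primary analyses. The same gap affects the 10% trigger, because it is unclear whether a filled outcome counts as recorded.

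**Working it through.** **1. The plan's own sample size.** Inputs from Sample size: ratio 0.8, coefficient of variation 0.9, 80% power, two-sided 5%.
- Log-scale SD = √ln(1 + 0.9²) = 0.770; difference = |ln 0.8| = 0.223.
- The t-test needs 189 per arm, so 378 per risk group and 756 in total.
- With 15% loss: 189/0.85 rounds up to 223, and 4 × 223 = 892.
- Pooled power is 97.8%.

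The stated figures reproduce. Power at 189 per arm is 80.4% by the normal approximation used below.

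**2. Bounding case by hand: peer mean only.** Assume equal weekday and weekend levels, a true ratio of 0.80 and a filled component of 0.9 in both arms, so that the filled part shows no arm difference.
- Weekday filled: (2 × 0.8 + 5 × 0.9)/(2 × 1 + 5 × 0.9) = 6.1/6.5 = 0.938.
- Weekend filled: (5 × 0.8 + 2 × 0.9)/(5 × 1 + 2 × 0.9) = 5.8/6.8 = 0.853.
- Overall log effect with a share f filled: (1 − f) ln 0.8 + f ln(ratio among the filled). For f = 5%, 10% and 20%, it shrinks by about 4%, 7% and 14% (weekday) or 1%, 3% and 6% (weekend).

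This ignores the own component, which the SAP names first, so it is a bound and not a description of the plan.

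**3. Simulation with the own component used.** There were 1,000,000 simulated participants per scenario. Assumptions:
- log-normal weekday and weekend SEDs, SD 0.77 each, with weekend 0.3 higher on the log scale;
- correlation between them 0.3 to 0.7;
- true ratio 0.80 on both day types;
- one component missing at random.

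The SAP gives none of the missing share, the correlation or the effect by day type. Power is at 189 per arm with the total SD held at 0.77.

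| Method without arm | 5% filled | 10% filled | 20% filled |
|---|---|---|---|
| Weekend filled, peer mean | 0.803 (79%) | 0.807 (77%) | 0.813 (74%) |
| Weekend filled, regression on own value | 0.801–0.803 (79–80%) | 0.802–0.804 (79–80%) | 0.804–0.809 (76–79%) |
| Weekday filled, peer mean | 0.805 (78%) | 0.811 (75%) | 0.823 (69%) |
| Weekday filled, regression on own value | 0.802–0.804 (79–80%) | 0.803–0.807 (77–79%) | 0.807–0.814 (74–77%) |
| Own value scaled by peer ratio | 0.80 (80%) | 0.80 (80%) | 0.80 (80%) |

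Entries are the estimated ratio and the power. Adding arm to the regression returns 0.80 and about 80% power in every scenario.

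**4. Which rows are plausible.** Ten consecutive days (consecutive wear is assumed) contain 6 to 8 weekdays and 2 to 4 weekend days. Losing every weekday while keeping a weekend day should be rare, so the weekend rows at low shares are the more realistic ones.

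**5. The two sections side by side.** Missing data fills a component so that a total can be formed. Primary efficacy analysis then takes complete cases of that total. A statistician may read complete as having a total, filled or not, or as having both components observed. Both readings fit the text.

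**The case against.** The best defence is that the plan does not impute from peers alone. The participant's own SED comes first, and it carries both the arm effect and the season of the same wear period. This stands: it makes the likely dilution small, and zero under ratio scaling. It does not remove the point, because the SAP does not commit to a method with no dilution.

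A reader might infer more than the documents support:

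- *That the effect shrinks by 4–14%.* Those figures come from the peer-mean bound with the weekday part missing. The SAP does not describe that method, and that pattern of missing days is the less likely one.
- *That leaving out season pulls the arms together.* Season should balance under randomisation, so its omission mainly adds noise. The 12-month wear also falls at about the same time of year as the baseline SED in the ANCOVA.
- *That the fill is single and the confidence interval therefore too narrow.* The SAP says neither single nor multiple. The concern about the interval applies only if a single fill is used.
- *That peers are drawn from 64 sparse cells (2 × 2 × 2 × 8 states and territories).* The wording fits a regression on main effects equally well.
- *That the two sections contradict each other.* Filling a component to form a score can coexist with a participant-level complete-case analysis. The SAP does the same for the MHI-5, where up to two items may be imputed. What is missing is an inclusion rule.

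It is also fair to say that filling a baseline component without arm does no harm, since baseline wear precedes randomisation. The point concerns the 12-month value only.

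**Conclusion.** The point holds, with moderate weight. The listed imputation variables omit randomised arm, which is the contrast the primary model estimates. With the same effect and the same log-scale spread on both day types, as assumed here, the result is no change or a shift toward no difference.

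With a true ratio of 0.80 and 5–10% of participants lacking one component, the estimate is about 0.801–0.807 and power 77–80% when the own value enters a regression. A pure peer mean gives up to about 0.81 and power down to 75%. All of this depends on the assumed missing share, on the assumed correlation and on missingness at random. The power figures also ignore any gain from baseline adjustment.

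Omitting date of wear costs precision rather than validity. Separately, the status of filled participants in the primary ANCOVA is unresolved. This does not amount to a must-fix flaw: any bias is conservative, small at plausible shares and possibly nil. It is nonetheless avoidable at almost no cost, and it concerns the primary estimate.

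**What to change.** Amend the SAP before analysis:

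1. For the 12-month outcome, name the imputation model. Include randomised arm (or impute within arm), date or month of wear, baseline log SED, the participant's own observed component and the four factors already listed. Because the primary effect is estimated separately by phenotypic risk group, fit the model within each group or include an arm-by-risk-group term.
2. Use multiple imputation, form the weighted total in each completed data set, and combine with Rubin's rules, so that imputation error reaches the confidence interval.
3. State whether participants with one imputed component belong to the primary analysis set, and whether they count as having the outcome recorded for the 10% trigger. Use one trigger and one denominator in both sections.
4. Report the other choice as a sensitivity analysis: both components observed if the primary set includes imputed participants, or imputed participants included if it does not.

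The cost is SAP wording, modest programming and a slightly wider interval. No new data are needed, since the dosimeters are time-stamped.
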